**Figure 3 figure3:**
[figure not shown]
Randomization and allocation of intervention and enhanced standard of care in Mentor Moms+ Study, South Africa.

#### RCT Outcomes

The RCT primary outcome is the preliminary effectiveness (comparing the MM+ arm to the enhanced HIV attention control arm using intention-to-treat analysis) defined as a reduction in alcohol use via biomarker-confirmed self-reported and biological samples (comparing baseline to 6 months in phosphatidylethanol [PEth] blood samples).

Secondary outcomes include (1) PrEP initiation and adherence (via patient records and urine TFV testing at 6 months) and (2) ART adherence (via urine TFV testing and self-report). In addition, we will evaluate three of the eight implementation outcomes, as defined by Proctor et al [46]: feasibility, acceptability (including participant satisfaction with the intervention), and fidelity. We will also track any social or health harms in the study and relatedness to the study intervention through study surveys and review of medical records. Table 2 describes how these outcomes will be measured. We will track session attendance, as well as ART and PrEP adherence, at each study visit.

**Table 2 table2:** Description of aim 3 implementation outcomes.

Evaluation parameter	Description	Methods	Frequency
Theoretical model	Evaluate changes in alcohol use and HIV prevention or treatment (eg, PrEP^a^ and ART^b^ use) using the theory-of-change model measuring change and which sociodemographic and behavioral characteristics are associated with change in order to understand any subpopulations receptive toward the strategic priorities and pathways of change identified by our model.	Quantitative surveys at each visit and biomarker data	Baseline and 6-month follow-up
Participants’ self-reported fidelity	Evaluate completeness of the intervention through a checklist assessing whether specific topics were covered during intervention sessions, including an assessment of the quality of intervention interactions, where participants will rate implementer engagement during intervention sessions.	Quantitative surveys at each visit and biomarker data	Baseline and 6-month follow-up
Acceptability and uptake of and satisfaction with the intervention	Evaluate the organizational, provider, and PLW^c^ acceptability of the intervention, including the number and percentage of sessions attended and IDI^d^ feedback following the sessions. Success would be >80% of sessions attended with very good/good feedback postsessions.	Mixed methods	Postimplementation mixed methods: 6-month survey (all participants), followed by IDIs with 20 providers and 20 participants
Fidelity to training assessment	Evaluate sessions (20% recorded and reviewed by the principal investigator) and fidelity to training using a checklist of key parameters. Success would be >80% of sessions supervised following training SOPs^e^.	Monitoring forms: comparison of SOPs and audio-recorded MM+^f^ sessions	Postimplementation mixed methods: 6-month survey (all participants), followed by IDIs in 20 providers and 20 participants
Feasibility of the intervention	Evaluate organizational, provider, and PLW views on the feasibility and scalability of the implementation of the intervention.	Mixed methods	Postimplementation mixed methods: 6-month survey (all participants), followed by IDIs in 20 providers and 20 participants

^a^PrEP: pre-exposure prophylaxis.

^b^ART: antiretroviral therapy.

^c^PLW: pregnant and lactating women.

^d^IDI: in-depth interview.

^e^SOP: standard operating procedure.

^f^MM+: Mentor Mothers Plus.

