**Methods:**

Using the ADAPT-ITT (assessment, decision, adaptation, production, topical experts, integration, training, testing) framework, we adapted the evidence-based Mentor Mother (MM) model, originally aimed at reducing vertical HIV transmission among mothers with HIV. Our mixed methods design includes (1) qualitative research, including in-depth interviews (IDIs) and focus group discussions (FGDs), to assess drivers of perinatal alcohol use and HIV risk; (2) intervention adaptation through community-based participatory workshops with stakeholders to refine the MM+ intervention in order to include culturally and contextually strategies; and (3) a pilot RCT with 100 pregnant women (≥16 years old, reporting recent alcohol use) randomized in a 1:1 ratio to the MM+ intervention (motivational interviewing [MI], including HIV and alcohol reduction messaging) or enhanced standard of care (SOC). Primary RCT outcomes include reduced alcohol use, via phosphatidylethanol (PEth) blood levels at 6-month follow-up. Secondary outcomes include uptake and adherence to pre-exposure prophylaxis (PrEP) and antiretroviral therapy (ART) among women with HIV, as well as intervention fidelity, feasibility, and acceptability.

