#### Outcome Data Ascertainment

Participants will be followed for 6 months. During this time, they will have three study visits, in which they will self-report alcohol use and PrEP or ART initiation or continuation to study staff. At each study visit, we will ascertain dried blood spots for assessment of recent alcohol use, via PEth testing (PEth<20 ng/mL represents light or no consumption [47]) and AUDIT-C, a validated survey of alcohol use (0=abstinence, >0=recent alcohol use). Participant medical files will be reviewed at the end of the study to ascertain birth outcomes (including any pregnancy loss or stillbirth), reported harms, and PrEP and ART prescription. At each study visit, participants will provide a urine sample to the study staff for analysis of recent PrEP or ART use using urine TFV testing (of recent adherence in the past 72 hours). Urine TFV results will show recent adherence and will be evaluated in conjunction with viral loads (VLs). For those on ART, we will review their files for VLs to evaluate VL suppression at baseline and end of the trial (VL<200 copies/mL). If VLs are unavailable, we will track them online with the national health laboratory service.

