### RCT Inclusion Criteria

Women who are ≥16 years old, with a confirmed pregnancy; who report alcohol use during pregnancy (in the past 2 months); who live within 20 km of the study facility; and who are able and willing to consent to study participation are eligible to participate.

One trained research assistant based at the ANC clinic will screen and obtain informed consent from PLW during their routine ANC visits using a set script for screening participants. We have received a waiver of parental consent for adolescents aged 16 and 17 years.

We will randomize the enrolled participants who have provided informed consent to the MM+ intervention or to enhanced HIV attention control in a 1:1 ratio. Randomization will be performed immediately following enrollment using dynamic permuted blocks with REDCap randomization sequentially. Trained researchers will not have access to the random allocation sequence. The intervention is nonblinded.

All study procedures will be in a private space in the Saldanha Bay municipality clinics, including screening, review, and signing of consent forms, surveys, and other procedures. This space will be dedicated research space given to the Human Science Research Council (HSRC) and FARR teams. We will ask pregnant women who may be interested in the study to see the study staff (in the study room) at the end of their visits or to get an appointment for another day to return to the clinic for study enrollment (if eligible).

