#### Power Calculations

We calculated power based on a 20% or more reduction in alcohol use in the intervention arm compared to no reduction (or minimal <5% reduction) in the control group. By enrolling 100 pregnant women (n=50, 50%, per arm), our study will be adequately powered at >80% for all primary effectiveness outcomes of feasibility and reduction in alcohol use. In qualitative work, the sample size is determined by the number of interviews expected with a specific population to reach thematic saturation [50,51].

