#### Descriptive Analysis and Effectiveness Outcomes

We will use basic measures (proportions, means and SDs, medians and IQRs, as appropriate) and graphical displays to describe distributions of key variables. Bivariable analyses will use Student's *t* tests (replaced by Mann-Whitney U tests for nonnormal distributions) or chi-square tests (replaced by exact tests for sparse data), as appropriate. We will compare study arms’ descriptive statistics without tests of statistical significance. Comparisons of randomized groups’ primary analyses will be by intention to treat, with secondary analyses based on intervention uptake. Specifically, we will evaluate reductions in alcohol use from baseline to 6-month follow-up in PEth levels, with confirmation of self-reported AUDIT-C scores compared by study arm. For secondary HIV outcomes, we will evaluate ART and PrEP adherence by study arm using urine TFV levels for recent adherence and VLs at 6 months for women on ART.

All statistical tests will be two-sided at α=.05; all effect estimates will be reported with 95% CIs. For both aims, we propose a priori subgroup analyses by age and HIV status. For subgroup analyses, effect modification will be assessed from the fully adjusted model on the additive scale by calculating the relative excess risk due to interaction [54] and on the multiplicative scale by examining the interaction term in regression models. Data will be analyzed in Stata version 15.

We will track missing variables in our monthly quality control and follow-up on all missing exposures and outcomes at each visit. We will conduct sensitivity analyses, including multiple imputation, to include evaluation outcomes and exposures from missing data and incomplete retention. Our retention efforts will focus on retention in both groups to ensure that there is no differential loss to follow-up. Analysis of implementation outcomes will entail descriptive summarization of acceptability, feasibility, and fidelity of MM+, including for women of different socioeconomic statuses or education levels.

Data management procedures will be developed with the statistical analysis plan and available upon demand to study investigators.

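### The primary outcome is stated inconsistently: self-report, level versus change, and the status of feasibility differ between sections

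*Protocol article*

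**What the plan says.** The protocol article describes the primary outcome in four places.

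- Abstract, Methods: "Primary RCT outcomes include reduced alcohol use, via phosphatidylethanol (PEth) blood levels at 6-month follow-up". Self-report is not mentioned. The secondary outcomes listed there end with "as well as intervention fidelity, feasibility, and acceptability".
- RCT Outcomes: a single primary outcome, defined as "reduction in alcohol use via biomarker-confirmed self-reported and biological samples", followed by a parenthesis that compares baseline with 6 months in PEth blood samples. Feasibility is one of three implementation outcomes evaluated in addition to the secondary ones.
- Power Calculations: the trial is called "adequately powered at >80% for all primary effectiveness outcomes of feasibility and reduction in alcohol use".
- Descriptive Analysis and Effectiveness Outcomes: the analysis will evaluate "reductions in alcohol use from baseline to 6-month follow-up in PEth levels, with confirmation of self-reported AUDIT-C scores", compared by arm.

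The Outcomes paragraph of the Analysis Plan again places feasibility among the implementation outcomes. Outcome Data Ascertainment says that women report their drinking to study staff. It takes PEth below 20 ng/mL to cover both light drinking and none, and takes any AUDIT-C score above 0 as recent use. RCT Inclusion Criteria states: "The intervention is nonblinded". Limitations accepts that social desirability may still affect self-report.

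**The concern.** The primary outcome decides what the trial may conclude, and three of its features change with the section that is followed: whether self-report is part of it, whether PEth is taken as a 6-month level or a change from baseline, and whether feasibility is also primary. An analyst who has seen the data could find support in the article for more than one choice.

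Self-report matters most. The women know their arm, and the MM+ arm receives repeated motivational interviewing on alcohol. Women counselled to drink less may be more inclined to report that they do. If their answers form part of the primary outcome, a difference in reporting can look like a difference in drinking. A PEth-only comparison is not open to that.

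**Working it through.** **1. The statements side by side**

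| Section | Self-report in the primary outcome? | PEth as level or change? | Feasibility |
|---|---|---|---|
| Abstract, Methods | No | Level at 6 months | Secondary |
| RCT Outcomes | Yes, by its wording; the parenthesis names PEth only | Baseline compared with 6 months | Implementation outcome |
| Power Calculations | Not stated | A reduction; scale not stated | Primary effectiveness outcome |
| Descriptive Analysis and Effectiveness Outcomes | AUDIT-C attached as confirmation; unclear which measure confirms which | Reduction from baseline | Described only |
| Analysis Plan, Outcomes | Not addressed | Not addressed | Implementation outcome |

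PEth at 6 months is common to all the alcohol versions. The other features are not settled. In Table 2, acceptability and fidelity each carry a success mark above 80%. The feasibility row collects views and has no mark, so there is no hypothesis about feasibility for which power could be computed.

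**2. The stated power depends on the missing scale**

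Inputs from Power Calculations: 50 women per arm, and a fall of at least 20% with MM+ against none, or under 5%, in control. The two-sided 5% level comes from the analysis section. The scale is not given, so the figure above 80% can be reproduced only reading by reading.

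*Proportion of women who reduce or stop.* Power = Φ{[|p1 − p2| − 1.96√(2p̄(1 − p̄)/n)] / √[(p1(1 − p1) + p2(1 − p2))/n]}.
- 20% v 0%: (0.20 − 1.96 × 0.0600)/0.0566 = 1.46, power 92.7%.
- 20% v 5%, the upper bound: (0.15 − 1.96 × 0.0661)/0.0644 = 0.32, power 62.4%.

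*Mean log PEth, 20% lower with MM+.* The difference is −ln(0.8) = 0.223, and power = Φ{0.223/(SD√(2/50)) − 1.96}. The SD is an assumption.
- SD 0.4: 79.7%. SD 0.5: 60.7%. SD 1.0: 19.9%.
- 80% power needs an SD of about 0.40 or less.

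The claim is met on some readings and not on others, so the scale is part of the definition that has to be fixed.

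**3. Where self-report could let bias in**

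A woman who reports no drinking but has PEth of 20 ng/mL or more is contradicted by the biomarker. Below 20 ng/mL, PEth does not separate light drinking from none, so a reported zero cannot be checked.

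*Illustration only.* Assume that success means PEth below 20 ng/mL and AUDIT-C of 0, a rule that the article does not state. Assume no true effect, a share q of both arms with PEth below 20 ng/mL, and that 50% of those women report zero in control against a share s in MM+. The spurious difference is q(s − 0.50). The chance of a significant result favouring MM+ uses the first formula above with n = 50 per arm.

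| q | s | Spurious difference | Chance of false positive favouring MM+ |
|---|---|---|---|
| 0.3 | 0.6 | 3 points | 6.0% |
| 0.4 | 0.6 | 4 points | 7.0% |
| 0.4 | 0.7 | 8 points | 15.2% |
| 0.4 | 0.8 | 12 points | 27.5% |
| 0.5 | 0.8 | 15 points | 35.8% |

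The nominal chance in that direction is 2.5%. If PEth alone is analysed, the spurious difference from reporting is zero.

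**The case against.** The strongest reply is that the alcohol outcome is coherent in substance. All versions rest on PEth at 6 months. The parenthesis in RCT Outcomes names only PEth, and the analysis section evaluates PEth levels with AUDIT-C as corroboration. The Abstract says that its outcomes include PEth, so its silence on self-report excludes nothing. The trial is a 100-woman pilot, and a separate analysis plan may hold the rules for discordant results. Strengths presents biomarker plus self-report as deliberate, and Limitations notes that biomarkers may miss drinking patterns.

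Much of this stands. A PEth-change reading is available, and it would be wrong to call the alcohol versions incompatible. But the wording before the parenthesis does include self-report, confirmation has no stated direction, and level and change are not reconciled. A rule for discordant results can be left to the analysis plan; conflicting statements of the primary outcome in one article cannot. The reply does not touch feasibility.

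The difference in alcohol content between the arms is also less clear than it first appears. The section on the pilot RCT's design describes standard of care as having no alcohol messaging. A sentence on benefits under Enhanced Standard of Care can be read as saying that counselling in both arms addresses alcohol. Blinding of the outcome interviewers is not stated either way. The bias route therefore rests on nonblinded women reporting their own drinking, with alcohol-focused interviewing described for MM+.

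**Conclusion.** The inconsistency is real. The article leaves open whether self-report belongs to the primary outcome and whether PEth is a level or a change. It also calls feasibility a primary effectiveness outcome with more than 80% power, against its own text elsewhere and with no threshold to test.

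Differential reporting is a reason to keep self-report out, not a demonstrated bias. Its size cannot be derived from the documents, and the table above rests on an assumed success rule and assumed reporting rates.

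Three stronger readings are tempting and not supported:
- A definite bias of some number of points. No section defines success as low PEth together with a zero AUDIT-C score.
- That the two measures cannot confirm each other. PEth of 20 ng/mL or more can refute a reported zero, and a positive AUDIT-C with PEth below 20 ng/mL is no conflict, because that range includes light drinking. Only a reported zero with low PEth goes unchecked.
- That the AUDIT-C recall period would make every woman positive at 6 months. No recall period is given, and one of 6 months would reach back only to baseline.

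**What to change.** State one primary outcome in the same words in the Abstract, RCT Outcomes, Power Calculations and the effectiveness analysis: PEth at 6 months, compared between arms by intention to treat, on one named scale. The log PEth level adjusted for baseline PEth is one suitable choice, and it settles level against change.

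- Take the self-report wording out of the primary definition in RCT Outcomes.
- Make AUDIT-C a secondary outcome, reported with a PEth/AUDIT-C discordance table by arm.
- Remove feasibility from the primary effectiveness outcomes and from the power statement, and keep it as an implementation outcome.
- Restate the power on the chosen scale, with its assumptions.

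The definition should be settled before outcome data are analysed. No further data need be collected. The price is that AUDIT-C loses primary status, and that the power figure may not hold once the scale is fixed: on an unadjusted log scale it needs an SD of about 0.40 or less.

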#### Outcome Data Ascertainment

Participants will be followed for 6 months. During this time, they will have three study visits, in which they will self-report alcohol use and PrEP or ART initiation or continuation to study staff. At each study visit, we will ascertain dried blood spots for assessment of recent alcohol use, via PEth testing (PEth<20 ng/mL represents light or no consumption [47]) and AUDIT-C, a validated survey of alcohol use (0=abstinence, >0=recent alcohol use). Participant medical files will be reviewed at the end of the study to ascertain birth outcomes (including any pregnancy loss or stillbirth), reported harms, and PrEP and ART prescription. At each study visit, participants will provide a urine sample to the study staff for analysis of recent PrEP or ART use using urine TFV testing (of recent adherence in the past 72 hours). Urine TFV results will show recent adherence and will be evaluated in conjunction with viral loads (VLs). For those on ART, we will review their files for VLs to evaluate VL suppression at baseline and end of the trial (VL<200 copies/mL). If VLs are unavailable, we will track them online with the national health laboratory service.

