### Study Design for the Pilot RCT (January 2026-February 2027)

We will identify and train 3-5 mentor mothers from the community. Inclusion criteria for mentor mothers include women (≥25 years old) in the community with lived experience who are either on PrEP or have HIV and are on ART and who reported reducing or stopping using alcohol during pregnancy. Mentor mothers will be trained on the adapted MM+ curriculum and MI techniques (step 7 of ADAPT-ITT). We will include 10-15 providers (midwives, nurses, and counselors) to be part of the MM+ training and support the integration of MM+ in three antenatal care (ANC) clinics. Concomitant ante- and postnatal care, including HIV testing and ART and PrEP provision, will be provided to all women regardless of study allocation.

Following training, trained study staff in three local clinics and surrounding communities will recruit and enroll 100 pregnant women who report recent (past 2 months) alcohol use to evaluate the effectiveness and feasibility of the MM+ intervention in reducing alcohol use in PLW, PrEP use in PLW without HIV, and ART adherence in PLW with HIV (step 8 of ADAPT-ITT). Participants will be randomized in a 1:1 ratio to the MM+ study arm or enhanced standard of care (SOC). SOC is focused on HIV counseling by peers, without alcohol messaging. If we are unable to identify 100 women in the three select clinics and communities, we will expand to additional communities and clinics.

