### Enhanced Standard of Care

Given that existing MM models focus on vertical HIV transmission and HIV prevention and treatment, and our primary aim is to understand how inclusion of alcohol reduction strategies reduces alcohol use and improves adoption of ART/PrEP use, we will use enhanced SOC with the same time frame for the intervention (eg, two to three sessions during antenatal and two to three sessions during postpartum periods). This will consist of educational counseling delivered by peers (mentor mothers) on HIV risk, partner testing modalities, and PrEP/ART urine assay testing, followed by real-time in-clinic adherence counseling delivered privately (one on one) by mentor mothers (separate from intervention mentor mothers to avoid contamination), all coinciding with routine ANC visits when possible.

Benefits of the study include counseling and support from lay counselors (in SOC) and mentor mothers (in the intervention) to address alcohol use and HIV prevention and care. Risks include unintended disclosure of alcohol use or HIV status by providers or staff and potential breaches of confidentiality that could cause social harms, including IPV. We will train staff and providers to ensure they are aware of these risks and do not share details of participants’ status outside of the study. We will monitor all social and other study harms throughout the study through regular surveys and review of medical records.

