### Analysis Plan

#### Outcomes

The implementation outcomes include feasibility (provider, organizational, and participant feedback), acceptability (number of sessions attended, feedback on content), and fidelity to study SOPs on MM+. The safety outcomes include IPV and pregnancy and birth outcomes (including preterm birth, birth weight, and miscarriage or stillbirth and infant survival) [48,49].

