We will use phone calls and text messages for follow-up to improve retention. Text messages will be neutral and not contain personal information about the participants (eg, appointment reminders will say, “Your appointment is on Tuesday at 3:00 p.m.”). At each visit, staff will ask about social harms, complete a detailed report, link the participants to community resources for support, and report social harms to the ethics review board. If multiple social harms are observed, the study procedures and text message content will be reviewed by the study team and CABs and recommended changes submitted to regulatory bodies for review.

All data collection procedures, regardless of the source, will follow standardized procedures outlined in the *Manual of Operating Procedures*, with individual activities guided by SOPs. RCT data (aim 3) will be collected by trained study interviewers using REDCap electronic software, which is Health Insurance Portability and Accountability Act (HIPAA)– and Protection of Personal Information Act (POPIA)–compliant for research studies. The interviewers will ask questions and complete the responses using a handheld tablet with internet connectivity for rapid data access and quality control.

The Data Safety and Monitoring Board (DSMB), which will comprise experts in the field of HIV and substance use in pregnancy, will be formed in the first year of the study and will meet quarterly to evaluate safety outcomes and data monitoring. A CAB was formed in 2025 that includes pregnant individuals, health care providers, and community leaders from Saldanha Bay and has held two meetings to date. CAB members are supporting the study by providing input, guidance, and feedback on the study’s methodology and implementation throughout the study period, ensuring community perspectives are considered.

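### The timing of medical-file review conflicts between sections, and for pregnancy and birth outcomes the only named source comes at the end of the study, too late for some or all quarterly DSMB meetings

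*Protocol article*

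**What the plan says.** Five places in the protocol article bear on this.

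- **Outcomes (Analysis Plan)** defines safety: "The safety outcomes include IPV and pregnancy and birth outcomes (including preterm birth, birth weight, and miscarriage or stillbirth and infant survival").
- **Ethical Considerations** sets up a DSMB that "will meet quarterly to evaluate safety outcomes and data monitoring". It also provides for social harms: "At each visit, staff will ask about social harms, complete a detailed report".
- **Outcome Data Ascertainment** sets the source and timing for birth outcomes and reported harms: "Participant medical files will be reviewed at the end of the study to ascertain birth outcomes (including any pregnancy loss or stillbirth), reported harms". The same section states "Participants will be followed for 6 months", with three study visits in that time.
- **Enhanced Standard of Care** gives a different timing for harms: "We will monitor all social and other study harms throughout the study through regular surveys and review of medical records".
- **RCT Outcomes** names the same two sources, surveys and patient files, without a timing: "We will also track any social or health harms in the study and relatedness to the study intervention through study surveys and review of medical" […].

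**The concern.** Quarterly safety review is useful only if the safety outcomes exist when the board meets. The article gives the board that task and counts miscarriage, stillbirth, preterm birth, birth weight and infant survival among the outcomes. Yet the section that says how data are obtained puts the file review at the end of the study. A site that follows that section opens no file for birth outcomes until then. A site that follows Enhanced Standard of Care reads records all along, at least for harms. The article does not say which instruction governs, or whether birth outcomes count among the other study harms mentioned there.

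The most serious safety outcomes in the list are at stake. Under the end-of-study timing, a difference between arms in pregnancy loss, stillbirth or infant death that is visible only in the files would come to light late, possibly after follow-up has finished. Individual events would also be read late, when queries are harder to resolve.

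**Working it through.** The plan states no figure on this point that could be reproduced. The check compares the sections and then does simple calendar arithmetic.

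**Step 1: source and timing for each type of safety information**

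| Information | Source named | Timing stated |
|---|---|---|
| Social harms | Question at each visit; surveys and records | Each visit; throughout |
| Health harms in general | Surveys and records | Throughout (Enhanced Standard of Care); no timing (RCT Outcomes) |
| Reported harms from files | Medical files | End of study (Outcome Data Ascertainment) **against** throughout (Enhanced Standard of Care) |
| Pregnancy loss, stillbirth, other birth outcomes | Medical files | End of study; no other source named explicitly |

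The third row is a direct conflict. In the fourth row the only explicit timing does not serve the DSMB. I read preterm birth, birth weight and infant survival as covered by the birth-outcome review, because no other source is named for them.

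The wording of Outcome Data Ascertainment suggests that the timing was chosen. The section ties blood spots, AUDIT-C and urine to every study visit, and viral loads to baseline and trial end. The self-reports it lists for visits are alcohol use and PrEP or ART use. Pregnancy status is not among them.

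**Step 2: inputs for the calendar**

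- RCT window: January 2026 to February 2027, inclusive = 12 + 2 = 14 months (heading of the pilot RCT section).
- DSMB: one meeting per 3 months (Ethical Considerations).
- Follow-up: 6 months per woman (Outcome Data Ascertainment).
- Assumptions of mine: meetings are counted from the start of the RCT; enrolment is uniform over months 0 to 8, the longest period that leaves 6 months of follow-up (14 − 6 = 8).

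Meetings within the window: 14 / 3 = 4.7, so four, at about months 3, 6, 9 and 12.

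**Step 3: what the end-of-study review provides at each meeting**

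If the review is at each woman's exit, the share of women reviewed by month *t* is (*t* − 6) / 8, and zero for *t* ≤ 6.

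| Meeting | Review at trial close | Review at each woman's 6-month exit |
|---|---|---|
| Month 3 | 0% | 0% |
| Month 6 | 0% | 0% |
| Month 9 | 0% | 3/8 = 38% |
| Month 12 | 0% | 6/8 = 75% |

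The zeros in the last column do not depend on the enrolment pattern, since nobody can complete 6 months before month 6. The 38% and 75% do depend on it.

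**Step 4: delay for one event on the exit reading**

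A loss just after enrolment would be read up to 26 weeks later: 26 / 13 weeks per quarter = 2 meetings. This is the maximum, and later events wait less.

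**Step 5: the other reading**

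If Enhanced Standard of Care governs and its harms include birth outcomes, record-based information could be available at all four meetings. The article does not say that they are included.

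**The case against.** The strongest reply is that the two sections can be read together: harms are watched continuously, and a closing abstraction then fixes the final outcome data. That is ordinary practice. The text does not say that files are opened *only* at the end.

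There are other routes too. Surveys track health harms as well as social ones. Women in both arms have several counselling sessions before and after birth, and staff follow up by phone and text message. IPV, itself a listed safety outcome, is a social harm of the kind asked about at visits. Early meetings would have few births to consider on any schedule, and rare events among 50 women per arm are hard to interpret. Finally, this is a condensed article: operating procedures or a DSMB charter may settle how often files are pulled.

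Much of this stands. A reader might infer that all harms are collected only at the end and that the board would see no safety data during the trial. The documents do not support that, because record review throughout the study is stated for harms and social harms are asked about at each visit. Nor does it follow without conditions that none of the four meetings would have birth outcomes. That needs the end-of-study timing to govern alone and to mean trial close.

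Two things remain. The joint reading is plausible but not written down, and for birth outcomes it depends on an unstated meaning of other harms. Surveys, sessions and calls might pick up a loss, but none is named as a source for pregnancy outcome. A charter can set the format of reports; it cannot supply outcomes that have not yet been collected. The article states a timing that conflicts with another of its sections, so this is more than detail left to a fuller document.

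**Conclusion.** The concern holds as an inconsistency with a practical consequence, of moderate severity. On harms, two sections give different timings for the same source. On pregnancy and birth outcomes, the only explicitly named source is a file review at the end of the study, although the DSMB is to evaluate safety outcomes quarterly.

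If that timing is followed as written, file-ascertained birth outcomes are missing at all four meetings (trial-close reading), or at least at the first one or two, with partial data afterwards (exit reading). These counts rest on the 14-month window, on meetings counted from the start of the RCT and, for the partial percentages only, on uniform enrolment over 8 months. Visit-based social harms and survey-reported health harms are outside this finding.

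**What to change.** Amend Outcome Data Ascertainment so that it agrees with Enhanced Standard of Care:

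- State that each participant's medical file is reviewed for pregnancy loss, birth outcomes, infant survival and reported harms on a rolling basis, and in any case before each quarterly DSMB meeting.
- Keep the end-of-study review as the final reconciliation, and say whether that means trial close or each woman's 6-month exit.
- State that pregnancy and birth outcomes are included in the harms monitored throughout the study.

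The format of the DSMB reports can be left to its charter. No stopping rule or change in care is implied.

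The cost is a few sentences of protocol text and repeated short look-ups in at most 100 files, which the team already plans to open. If operating procedures not shown here already provide for rolling review, only the wording needs to change.
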